## **2. OBJECTIVES**

### **Primary objective**

We will assess whether EDB surgery will result in a significant reduction in the number of patients without vertigo spells at 12 months follow up, compared to patients who undergo a decompression operation.

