#### 8.1.2 Secondary study parameters

- Cumulative incidence of vertigo bouts
- Hearing
  - As defined in the diagnostic criteria of the Bárány Society (Lopez-Escamez, 2016), the following parameters will be assessed based on a three-tone audiometry at 0.5, 1 and 2 kHz (LFI):
    - The three-tone average score in decibels (dB), labelled as hearing threshold (HT).
    - Word recognition (WR), based on the speech discrimination. A decrease of  $\geq 10$  dB or a change in word recognition score of  $\geq 15\%$  points is considered clinically significant. When the pure-tone average and the WR change in the opposite direction, the pure-tone average score will be decisive to conclude the overall nature of change in hearing.
  - All pure tone audiometry analyses will be executed by the participating centre itself.
- Use of escape medication
  - The frequency and use of escape medication in the acute phase of vertigo will be recorded. This includes intratympanic injections and antivertigo medication.
- Co-interventions
  - Co-intervention is defined as performed ablative surgery during the follow up period because of unbearable vertigo bouts.
- Complications of surgery
- Functional Level Scale (FLS)
  - To assess the effect of the vertigo attacks on daily life, the 6-point FLS is recommended by the AAO-HNS for clinical trials in MD (Committee on Hearing and Equilibrium guidelines for the diagnosis and evaluation of therapy in Ménière's disease, 1995). One value is chosen to score the level of disability. The score will be reported as a total score, as

well as categorized into improvement, unchanged or worsened.

Categories will be based on the following definitions:

- Improvement: one or more points decrease on the FLS score compared to the baseline FLS score
- Unchanged: unchanged FLS score compared to the baseline FLS score
- Worsened: one or more points increase on the FLS score compared to the baseline FLS score.

- Dizziness Handicap Index (DHI)

- To evaluate the effect of vertigo in the patient's daily life the 25-item measure of the DHI is used which was developed by Jacobson and Newman (1990). This inventory is often used for follow-up of participants suffering from dizziness. Higher scores indicate more severe handicap. According to a review published in 2007 (Duracinsky 2007) it is a valid tool and could be regarded as a questionnaire of reference.
- The outcome is categorized as following:
  - 0-16 points: no handicap

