  - 16-34 points: mild handicap
  - 36-52 points: moderate handicap
  - 54+: severe handicap
- Categories will be based on the following definitions:
  - Improvement: the DHI score reflects at least 18 point improvement compared to baseline (Jacobson 1990).
  - Unchanged: the change in DHI score no greater than a 17 points increase of decrease compared at baseline.
  - Worsened: the DHI scores reflects a decrease of more than 17 points compared to baseline

- Tinnitus Handicap Index (THI)

- To quantify the effect of tinnitus on daily life, the THI is used. The scale is grouped into functional, emotional, and catastrophic subscales. According to literature, the THI is a reliable and valid tool for measuring the impact of tinnitus on the quality of life (Newman (1996)), Kleinstäuber (2014)). The Dutch version of the questionnaire that will be taken is validated (Vereeck L 2006) It uses the following grades of handicap due to tinnitus:
  - 0-16: Slight or no handicap (Grade 1)
  - 18-36: Mild handicap (Grade 2)
  - 38-56: Moderate handicap (Grade 3)

- 58-76: Severe handicap (Grade 4)
  - 78-100: Catastrophic handicap (Grade 5)
- Categories will be based on the following definitions:
  - Improvement: decrease in grade of THI at 6 and 12 compared to the baseline THI grade.
  - Unchanged: unchanged THI grade compared to the baseline THI grade.
  - Worsened: increase on the THI grade compared to the baseline THI grade.
- SF-36
  - The SF-36 encompasses eight health concepts: physical functioning, bodily pain, role limitations due to physical health problems, role limitations due to personal or emotional problems, emotional well-being, social functioning, energy/fatigue, and general health perceptions. It also includes an item that provides an indication of perceived change in health.

Scores are calibrated so that 50 is the average score or norm (Ware, 1993).
- EQ-5D VAS
  - The EQ-5D VAS records the respondent's self-rated health on a vertical, visual analogue scale where the endpoints are labelled 'best imaginable health state' and 'worst imaginable health state'.
- CEA

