|                      | Rinne left            | Positive
Negative                                             |
|                      | Dix Hallpike          | Positive
Negative                                             |
|                      | If positive: side:    | Left
Right                                                    |
|                      | Diadochokinesis       | Normal
Abnormal                                               |
|                      | If abnormal: side     | Left
Right                                                    |
|                      | Eye pursuit movements | Smooth
Abnormal                                               |
|                      | If abnormal: direct   | Left
Right
Up
Down                                      |

An MRI- and CT-scan will be performed and the patient is referred to a vestibular therapist. A PTA, vHIT and calorigram will be performed. Moreover, from the moment of inclusion, the patients starts reporting in de DizzyQuest App. This is a daily questionnaire of 31 questions addressing general functioning. In case of an attack, a short questionnaire is to be filled out. The inclusion and exclusion criteria will be double-checked by the coordinating investigator and if the patient does meet the criteria, the first survey package is sent through email. This survey pack consists of the HADS, DHI, THI, SF-36, EQ-5D VAS, NPQ, VADL, VAP and a questionnaire about expectations of the treatment.

All the pre-operative data is entered in Castor.

 The VAP and VADL are newly developed questionnaires to assess the effect of dizziness and/or balance problems on patients' ability to do things. They are not an outcome measure in this study, but we aim to anticipate on the possibility that the Bárány Society takes the outcomes of questionnaires into account in future studies. These questionnaires are taken for this trial as well, to enable comparison of the results of this study in the future that only use the VAP and the VADL.

In the following weeks, the patient visits the vestibular therapist, who takes the medical history and performs the first measurements. The patient is seen by the anaesthetist for regular pre-operative screening.

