### 15.3 Appendix 3 – Full vestibular rehabilitation therapy

All patients in this study will receive vestibular rehabilitation after surgery. It is assumed that all patients suffer from dizziness and accompanied problems like balance, visual and gait deficits, because of inner ear hydrops and hypofunction of the labyrinth. Stable hypofunction of the labyrinth can be trained by vestibular rehabilitation (Hillier 2016) and is considered to be a valuable addition to the surgery. Until now literature showed no conclusive evidence of beneficial effects of vestibular rehabilitation in patients with MD (Van Esch 2017). The lack of evidence can be attributed to the low quality of the studies, but possibly it could be less effective due to the fact that vestibular rehabilitation should be preserved for patients with stable vestibular lesions (Clendaniel 1997, Shepard 1990). In this study it can be expected the lesion is stable after surgery and vestibular rehabilitation is effective. Practical experience supports this rationale. Patients who have undergone decompression surgery could still have unstable vestibular function.

Goal of vestibular rehabilitation is to achieve a reduction of patient's specific vestibular functional deficits. The following specific goals per deficits are:

- Reduction of complaints of dizziness measured with the DHI (at least 12 points reduction) within 3 months.
- Maximize gaze stabilization (DVAT-NI), compared with norm values or reaching a plateau for 6 weeks, within 3 months.
- Optimize balance ((sharpened) Romberg, one leg stance test), in which we strive to meet norm value or reaching a plateau for 6 weeks, within 3 months.
- Optimize gait (DGI), in which we strive to have an effect of 4 or more points or reach the maximum score within 3 months.

An experienced and skilled vestibular therapist will perform a functional assessment and make an individual tailored program for each patient. Preferably the therapist is associated with one of the participating centers. The therapist should be trained in vestibular rehabilitation by one of the following courses: basic course or masterclass of Apeldoorns Duizeligheidscentrum (ADC), Nederlands Paramedisch Instituut (NPI) course 'fysiotherapie bij perifeer vestibulaire duizeligheid' or NPI masterclass 'Advanced Rehabilitation for Vestibular disorders and cervicogenic dizziness. Besides training a therapist should treat at least 10 patients with vestibular rehabilitation.

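### The DHI 'worsened' category is defined in the wrong direction, so large improvements are classed twice and large deteriorations not at all

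*Protocol*

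**What the plan says.** **DHI.** Protocol section 8.1.2 fixes the direction of the scale: "Higher scores indicate more severe handicap". It then gives three change categories:

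- For a participant who gets better, the rule is "Improvement: the DHI score reflects at least 18 point improvement compared to baseline".
- For a participant who stays about the same, it is a band that runs equally far both ways: "Unchanged: the change in DHI score no greater than a 17 points increase of decrease compared at baseline".
- For a participant who gets worse, which is the rule at issue here, it is "Worsened: the DHI scores reflects a decrease of more than 17 points compared to baseline".

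Appendix 3 sets a DHI goal for vestibular rehabilitation: "Reduction of complaints of dizziness measured with the DHI (at least 12 points reduction) within 3 months". The DHI severity bands in 8.1.2 begin 0-16 (no handicap) and 16-34 (mild).

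**FLS.** The same section defines FLS improvement as "one or more points decrease on the FLS score compared to the baseline FLS score"; unchanged and worsened are also relative to baseline. For the preoperative stage, section 8.3.1 states: "This survey pack consists of the HADS, DHI, THI, SF-36, EQ-5D VAS, NPQ", followed by the VADL, the VAP and an expectations questionnaire. The FLS is neither there nor in the table of baseline characteristics. Section 8.3.3 lists it at 3, 6 and 12 months.

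**Primary objective.** Section 2 will assess "whether EDB surgery will result in a significant reduction in the number of patients without vertigo spells at 12 months follow up". The Summary and the end of section 1 expect that number to be higher with EDB.

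**Analysis.** Section 10.2 treats patient-reported measures as continuous, presents categorical outcomes as counts with percentages, and assigns secondary outcomes to a linear mixed model.

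**The concern.** A responder classification should place each participant in exactly one category. Here the worsened rule points the same way as the improvement rule. If the rules are programmed as they stand, participants who gain clearly from surgery also appear among the worsened, and those who deteriorate clearly appear nowhere. In a surgical trial whose section 9.2.1 names worsening of vertigo as an adverse effect of the natural course, the deteriorations are the cases a reader would look for. If the analyst instead corrects the rule silently, the published categories depart from the protocol without a record.

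The FLS raises a different question. Its definition is sound, but it needs a measurement that the visible schedule does not list. A preoperative score that was never taken cannot be recovered after surgery.

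**Working it through.** The plan gives no figure to reproduce. The check applies the stated rules and compares passages.

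**DHI.** Let d = follow-up score minus baseline score, in whole points. Higher is worse, so a negative d is better. The rules in section 8.1.2 become:

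- Improved: d ≤ −18
- Unchanged: −17 ≤ d ≤ +17
- Worsened, as written: d < −17, which for whole points is d ≤ −18

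The first and third conditions are identical.

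| d | Category as written | If worsened is d > +17 |
|---|---|---|
| −40 | Improved and worsened | Improved |
| −18 | Improved and worsened | Improved |
| −17 | Unchanged | Unchanged |
| 0 | Unchanged | Unchanged |
| +17 | Unchanged | Unchanged |
| +18 | None | Worsened |
| +40 | None | Worsened |

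Every participant meeting the improvement rule also meets the worsened rule, and every rise of 18 or more is unclassified. With the direction reversed, each whole-number change falls in exactly one category.

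Could decrease here mean a decline in condition rather than in score? Three places in the protocol speak against it:

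- The line for unchanged, directly above, uses increase and decrease numerically for the DHI score.
- The neighbouring FLS and THI rules use decrease for improvement and increase for worsening.
- Appendix 3 treats a DHI reduction as the aim. Its 12-point figure is a rehabilitation target and is cited here only for direction.

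The severity bands have a separate slip: a score of 16 satisfies both 0-16 and 16-34.

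**FLS.** Counting assessments in the visible text gives 0 before surgery (section 8.3.1) and 3 after it (section 8.3.3, at 3, 6 and 12 months). The DHI and THI, the other two questionnaires with improved/unchanged/worsened categories, are both in the baseline pack.

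**Primary objective.** Section 4.4 plans on 95% attack-free with EDB and 70% with decompression, a difference of 95 − 70 = +25 percentage points. The wording in section 2 describes a negative difference. The test in section 4.4 is two-sided, and section 10.1 compares the numbers free of attacks, so neither depends on that word.

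**The case against.** The best defence is that the DHI slip is obvious and has limited reach. The improvement and unchanged rules together leave only one coherent meaning for worsened. Rules that put the same participant in two categories would probably prompt a query before any table was produced. Under section 10.2 the arms can be compared on the continuous DHI score, and categories are only tabulated. All of this stands, and it sets the size of the point. It does not remove it, because the protocol states the rule and states it wrongly.

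Three stronger readings are tempting, and the documents do not support them:

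- A reader might infer that the trial's DHI result would show benefit as harm, more so in the better arm. The mixed model on the score does not use the categories, and no figure in the protocol supports a difference between arms in the misclassification.
- A reader might infer that the FLS change outcome cannot be computed at all. Section 3 places the full list of questionnaires and tests in the Appendix 2 flow chart, which is not visible here, and section 8.1.2 presupposes that a baseline FLS score exists. The FLS is a single chosen value and need not come through the emailed pack. Only a conditional statement is justified.
- A reader might infer from section 2 that the primary hypothesis is reversed. The Summary, section 1 and section 4.4 agree on the intended direction, and the two-sided test is unaffected.

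**Conclusion.** The DHI worsened category is wrong as written and should be corrected. All falls of 18 points or more are classed twice, and all rises of 18 points or more are left out. The consequence is limited to a secondary change classification; the DHI score analysis and the primary outcome are unaffected. This conclusion rests only on the scale direction and the three rules in section 8.1.2.

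The FLS point is secondary and conditional. Section 8.3.1 lists no baseline FLS. If none is collected before surgery, the FLS change categories cannot be computed for any of the 74 planned participants, although the total score at follow-up can still be reported. If Appendix 2 does schedule it, section 8.3.1 is incomplete and should be brought into line.

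The primary objective needs an editorial correction only.

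**What to change.** 1. In section 8.1.2, define DHI worsened as an increase of more than 17 points (18 or more) from baseline. In the same edit, assign a score of 16 to one severity band only.
2. Check Appendix 2 for a preoperative FLS, and list the FLS at baseline in section 8.3.1. If it is not being collected, add it promptly, since this helps only participants not yet operated on.
3. In section 2, replace reduction with increase, to match the Summary, section 1 and section 4.4.

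The cost is a few wording edits through the usual amendment route and, if the FLS is not already collected, one more single-value item for participants before surgery. Sample size, primary test and follow-up schedule stay as they are.

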### 4.2 Inclusion criteria

In order to be eligible to participate in this study, a patient must meet all of the following criteria:

- Definite unilateral MD according to diagnostic criteria of the Bárány Society (Lopez-Escamez, 2016)
- More than 3 patient reported attacks in the 6 months prior to inclusion and at least 1 attack in the 2 months prior to inclusion
- Age  $\geq$  18 years at the start of the trial
- Non responding to a sufficient extent to conservative medical treatment including at least two sessions of at least one intra-tympanic injection (IT) each with corticosteroids (dexamethasone, methylprednisolone, triamcinolonacetonide)
- Dutch health care insurance

Definite MD according to Bárány Society:

- Two or more spontaneous episodes of vertigo, each lasting 20 minutes to 12 hours,

AND

- Audiometrically documented low- to medium-frequency sensorineural hearing loss\* in one ear, defining the affected ear on at least one occasion before, during or after one of the episodes of vertigo,

AND

- Fluctuating aural symptoms (hearing, tinnitus, or fullness) in affected ear (not better accounted for by another vestibular diagnosis).

\*Low frequency sensorineural hearing loss is defined as increases in pure tone thresholds for bone-conducted sound that are higher (i.e. worse) in the affected ear than the contralateral ear by at least 30 dB HL at each of two contiguous frequencies below 2000 Hz

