    - Assessment of static standing balance will be done by performing a Romberg, a sharpened Romberg and One Leg Stance Test. These tests are often used in the vestibular population (Gotshall 2011, Herdman 2014). Balance is a marker of vestibular function and it will be used as a guide in the vestibular rehabilitation. The results of the balance test will be compared with normative values (Gill-Body et al 2000, El Kashlan et al 1998)
    - The aim is to optimize balance ((sharpened) Romberg, one leg stance test), in which we strive to meet norm value or reaching a plateau for 6 weeks, within 3 months.
  - Gait

- Gait will be assessed using the dynamic gait index (DGI), an instrument to evaluate an individual's ability to modify balance during walking. This tool is a marker of vestibular function, as an intact VOR is required to perform the tests.
- The DGI contains 8 items which are all scored on a 4-point scale: 3 points for optimal score (no gait dysfunction), 2 points for minimal impairment, 1 point of moderate impairment and 0 points if there is a severe impairment in gait.
- Improvement in gait is defined as 4.0 points (Marchetti 2014) improvement on the total of 24 points possible, compared to baseline.
- Dynamic Visual Acuity
  - Dynamic Visual Acuity will be measured using DVAT-NI. DVAT-NI measures the gaze stability by assessing the vestibulo-ocular reflex (VOR) function in response to examiner generated rotational head movement stimuli (2 Hz) during reading lines of the ETDR chart (SLOAN). The DVAT-NI is used to screen and characterize the severity of gaze instability.
  - Patient with a score of two or more line difference between static and dynamic acuity is defined as having an abnormal DVA (Dannenbaum 2009). The DVAT-NI is a clinical used test and used as a guide to treatment (Dannenbaum 2005, Dannebaum 2009, Herdman 2014) and to treatment efficacy.

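### Several classification rules for secondary outcomes in section 8.1.2 do not work as written: THI categories without a common visit, a DHI score in two bands, and a DGI gain that is out of reach from a baseline of 21 or more

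*Protocol*

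**What the plan says.** **THI (8.1.2).** Scores are grouped into five grades: 0-16, 18-36, 38-56, 58-76 and 78-100. The first change category reads "Improvement: decrease in grade of THI at 6 and 12 compared to the baseline THI grade". The other two are worded without any visit. One is for patients whose grade has stayed where it was before surgery; the other is given as "Worsened: increase on the THI grade compared to the baseline THI grade".

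Section 8.3.3 collects the THI at 3, 6 and 12 months after surgery. Entry does not require tinnitus: section 4.2 asks for "Fluctuating aural symptoms (hearing, tinnitus, or fullness) in affected ear".

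**DHI severity (8.1.2).** The lowest band, no handicap, runs from 0 to 16. The next is "16-34 points: mild handicap".

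**DGI (8.1.2).** There are eight items, each scored 0 to 3. "Improvement in gait is defined as 4.0 points" on a total of 24, against baseline. Appendix 3 sets the rehabilitation goal for the same test: "Optimize gait (DGI), in which we strive to have an effect of 4 or more points or reach the maximum score within 3 months".

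**Analysis (10.2 and 10.2.2).** Patient-reported measures are assumed to be continuous and are summarised by means or medians at each time point. Categorical outcomes are given as counts and percentages of the whole group. All secondary outcomes go into a linear mixed model.

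**The concern.** A change category should place every patient in exactly one class at a named visit, and the improved class should be open to the patients counted in its denominator. The THI rule fails the first requirement, the DHI bands overlap at one score, and the DGI rule fails the second for patients near the ceiling. The THI rule has a similar floor: a patient in grade 1 has no lower grade to move to, and such patients can enter because tinnitus is not required.

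At stake is whether the tables of improved, unchanged and worsened patients can be produced without choices made after the data are seen, and whether a reader can interpret their percentages. The protocol's summary expects less tinnitus after duct blockage, so the THI table will be read.

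**Working it through.** **1. THI: which visit?** Let the grade at 6 and at 12 months each be lower than, the same as, or higher than baseline. That gives 3 × 3 = 9 patterns.
- *Joint reading (lower at both visits).* Only lower/lower is improved. Four patterns have a lower grade at exactly one visit: lower/same, lower/higher, same/lower and higher/lower. They fail the improvement rule. No visit is named on which to call them unchanged or worsened, and if those two categories are also judged over both visits, these patterns fit none of the three.
- *Visit-by-visit reading.* Each patient has exactly one category at 6 months and one at 12 months.
- On either reading, improvement is not defined at 3 months, although the THI is collected then.

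**2. THI: what does a grade shift measure?** The bands list even scores only, so steps of 2 points are implied. Going through all pairs of baseline and follow-up scores:
- Smallest fall that counts as improvement: 2 points, at four borders only (18 to 16, 38 to 36, 58 to 56, 78 to 76). The smallest rise that counts as worsening is also 2 points.
- Largest fall that stays unchanged: 36 − 18 = 56 − 38 = 76 − 58 = 18 points in grades 2 to 4, and 100 − 78 = 22 points in grade 5.
- From grade 1 (0 to 16), improvement is impossible.

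**3. DHI severity bands.** The bands are 0-16, 16-34, 36-52 and 54 or more. The first two share the score 16; the others do not overlap.

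**4. DGI ceiling.** The stated maximum reproduces: 8 items × 3 points = 24. The largest possible gain from baseline b is 24 − b.

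| Baseline DGI | Largest gain | 4.0-point rule reachable? |
|---|---|---|
| 20 | 4 | yes, just |
| 21 | 3 | no |
| 22 | 2 | no |
| 23 | 1 | no |
| 24 | 0 | no |

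A patient who goes from 22 to 24 meets the Appendix 3 goal but is not improved under 8.1.2. Because 10.2 takes percentages of the whole group, everyone starting at 21 or more stays in the denominator as a fixed non-improver.

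**5. How many patients?** This needs the baseline distributions of THI and DGI. The protocol gives neither, so no count follows.

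**The case against.** The strongest reply is that the categories are not the main comparison. Section 10.2 treats patient-reported measures as continuous, and 10.2.2 models all secondary outcomes across the measurement times, so the THI score, including month 3, is still described and compared. **This stands.** A reader might infer that the categories would hide a real difference between the arms. The documents do not support that: one rule applies to both randomised arms, and the score model does not depend on it. What 10.2.2 leaves unsaid is whether the score or the category enters the model, so it is worth stating.

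Second, the THI line need not require both visits; it can mean classification at each of them. **This also stands.** The defect is ambiguity, not a proven two-visit requirement.

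Third, the grades are presented as the scale's own, and any cut-off has borders. The documents give no minimal important THI difference, so a 2-point shift across a border cannot be called misclassification from the protocol, and replacing grades by a point margin would be a design preference. **Accepted.** One can simulate stable patients with baseline scores spread evenly over 0-100. With an assumed retest SD of 5, 8 or 10 points, about 16%, 25% or 31% change grade at one visit, in either direction. Neither the spread nor the SDs come from the protocol, so these figures do not measure the size of the problem.

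Fourth, a therapist's goal within 3 months and a trial outcome definition may legitimately differ, and a patient at 21 to 24 on the DGI is close to the top of the scale. **Accepted in part.** This is not a proven contradiction. The fixed non-improvers in the percentage remain, and the two wordings should be reconciled.

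**Conclusion.** The point holds as a set of faulty wordings in 8.1.2:
- The THI categories have no common visit. Read literally, they leave patients with a lower grade at only one of 6 and 12 months unclassified.
- One DHI score, 16, belongs to two severity bands.
- The DGI improvement rule cannot be met from a baseline of 21 to 24, and the THI rule cannot be met from grade 1.

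These follow from the text and from exact arithmetic; the only assumption is 2-point THI steps, which the bands imply. The size in patients is unknown. The consequence is limited to secondary descriptive tables: the primary endpoint is unaffected, and the planned between-arm comparison is a mixed model. Neither widespread misclassification nor a masked treatment effect is shown.

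**What to change.** Amend 8.1.2 before unblinding:

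1. **THI.** Define improved, unchanged and worsened separately at 3, 6 and 12 months, each against baseline, with 12 months as the main time point. State that the between-arm THI conclusion rests on the total score in the mixed model and that grade shifts are descriptive. Also show the proportion improved among patients with a baseline above grade 1.
2. **DHI severity.** Put the score 16 in one band only.
3. **DGI.** Keep the planned percentage and also report the proportion improved among patients with a baseline of 20 or less. Reconcile the definition in 8.1.2 with the goal in Appendix 3, or state that they serve different purposes.

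The DHI change rule should not serve as a model for the THI as it stands. It defines worsening as a fall of more than 17 points, although 8.1.2 says that higher DHI scores mean more severe handicap. That line needs correcting first.

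The cost is protocol wording, with no new data. The downside is smaller denominators, and so less precision, for the added proportions.
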